**Methods:**

This study comprises a randomised controlled multicentre trial with 1:1 allocation to an intervention and control group. In total, 520 employees with common mental disorders shall be recruited from companies being located around five study centres in Germany. Besides care as usual, the intervention group will receive up to 17 sessions of psychotherapy. The first session will include basics diagnostics and medical indication of treatment and the second session will include work-related diagnostics. Then, participants of the intervention group may receive work-related psychotherapeutic consultation for up to ten sessions. Further psychotherapeutic consultation during return to work for up to five sessions will be offered where appropriate. The control group will receive care as usual and the first intervention session of basic diagnostics and medical indication of treatment. After enrolment to the study, participants will be followed up after nine (first follow-up) and fifteen (second follow-up) months. Self-reported days of sickness absence within the last 6 months at the second follow-up will be used as the primary outcome and self-efficacy at the second follow-up as the secondary outcome. Furthermore, a cost-benefit assessment related to costs of common mental disorders for social insurances and companies will be performed.

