#### Sample size calculations

Sample size calculations were performed with PASS Version 16.0.3. Congruent with results of a recent uncontrolled trial, we expect that participation in psychotherapeutic consultation at work may reduce days of sickness absence from 36 days/6 months to 26 days/6 months at follow-up with a standard deviation of 35 days/6 months for both time points [73]. For the control group, we expect that days of sickness absence will increase from 36 days/6 months to 42 days/6 months due to the lack of work-related treatment in CAU [74] and possibly deterioration of health. The same standard deviation of 35 days/6 months will be expected for the control group. A negative binominal distribution of days of sickness absence will be expected in accordance with previous research [73]. Following those expectations, a dispersion parameter of 2.12 was calculated. To detect this difference with a power of 80% and assuming a two-tailed level of significance of 5%, a sample size of 310 participants with 155 participants for each group is required. Assuming dropout rates of 40% [15], 520 participants shall be recruited for the study in equal proportions per study centre.

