#### Statistical methods

The treatment effect on the primary outcome (days of sickness absence within the last 6 months at the second follow-up) will be analysed using a mixed negative binomial regression model. Treatment group, days of sickness absence within the last 6 months before baseline, gender, age, subjective work ability at baseline as well as the centre will be included as covariates and the respective company as random effect. The primary analysis will be conducted based on the full analysis set according to the intention-to-treat (ITT) principle (i.e. all patients will be analysed in the group they were randomised to).

Missing data for the primary and secondary outcome analysis is assumed to be “missing at random” and replaced using multiple imputation based on predictive mean matching using the covariates of the primary and secondary outcome analysis as potential predictors [75].

As a sensitivity analysis, an evaluation based on the per-protocol (PP) population will be performed. The PP set consists of all participants without major protocol violations. For this analysis, no imputation of missing data will be performed.

In case of significance of the ITT analysis of the primary outcome (two-sided confidence level of 5%), a hierarchical linear mixed model will be used to analyse treatment effects on self-efficacy. This model will include treatment group, self-efficacy at baseline, gender, age, subjective work ability at baseline as well as the centre as covariates and company as random effect. Applying this hierarchical testing strategy, the overall type I error rate will still be controlled.

If no significance of the ITT analysis is achieved, the results of this analysis will be interpreted only in a descriptive sense.

Furthermore, subgroup analyses will be performed to evaluate the role of additional variables (e.g. indication of treatment, type of treatment, symptom severity) on treatment effects on the primary and secondary outcome.

Further collected data (see Table 1) will be analysed using appropriate descriptive methods.

Details of the statistical analysis will be further determined in a statistical analysis plan which will be written before database closure.

All those analyses will be conducted using SAS 9.4 or higher.

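### The stated imputation predictors omit the named subgroup variables, so subgroup differences in treatment effect, if estimated on the imputed data, shrink by about the share of outcomes missing

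*Protocol article*

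**What the plan says.** All of this is in the protocol article, mostly under Statistical methods.

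- **Imputation.** Missing outcomes for the primary and secondary analyses are taken to be missing at random and are "replaced using multiple imputation based on predictive mean matching using the covariates of the primary and secondary outcome analysis as potential predictors".
- **What those covariates are.** The primary model has treatment group, sickness absence before baseline, gender, age, subjective work ability at baseline and centre, with company as a random effect. The self-efficacy model is the same with baseline self-efficacy in place of baseline absence. Treatment appears once, as a main effect.
- **Subgroups.** The section adds that "subgroup analyses will be performed to evaluate the role of additional variables (e.g. indication of treatment, type of treatment, symptom severity) on treatment effects", for the primary and secondary outcome. No dataset is named for these analyses.
- **Exemption.** Of the per-protocol analysis it says "For this analysis, no imputation of missing data will be performed". No other analysis is exempted.
- **Expected loss.** Under Sample size calculations: "Assuming dropout rates of 40% [15], 520 participants shall be recruited for the study in equal proportions per study centre".

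**The concern.** An imputation model should be at least as rich as the analysis it feeds. Here the predictors match the main models but are narrower than the subgroup models. An outcome imputed without knowledge of the subgroup cannot carry a treatment effect that differs by subgroup, except so far as the listed covariates stand in for it. Pooling such outcomes with the observed ones pulls the estimated difference towards zero. No departure from missing at random is needed.

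Differing effects are plausible by design. Under Module 2, participants with an ICD-10 diagnosis receive module 2-A and subclinical participants module 2-B. PHQ-9 level is a stratification factor under Allocation but is not an imputation predictor. The risk is a report that the effect is much the same across severity when part of that sameness comes from the imputation.

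**Working it through.** **The plan's own figure.** The sample size section states that "a sample size of 310 participants with 155 participants for each group is required". Inflating for 40% dropout gives 310 / (1 − 0.40) = 517. The stated 520 is this rounded up to 104 in each of five centres. The implied missing share is 1 − 310/520 = 40.4%, so 40% is the right planning value.

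**Analytic check.** Let δ be the true difference in treatment effect between subgroups and m the share of outcomes imputed. Observed outcomes carry δ and imputed ones about 0, so the pooled estimate is about (1 − m)δ. With m = 0.40 this is 0.60δ; with m = 0.20 it is 0.80δ.

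**Simulation A, days scale.** The plan gives 520 randomised, 40% missing, and means of 42 days (control) and 26 days (intervention). Assumed: two equal subgroups with intervention means 34 and 18 (average 26), outcome capped at 130, missing completely at random. There were 500 trials, 5 donors and 10 imputations.

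| Analysis | Subgroup difference in effect (days) | Ratio to full data |
|---|---|---|
| Full data | −15.12 | 1.00 |
| Observed outcomes only | −15.26 | 1.01 |
| Imputed as written | −9.22 | 0.61 |
| Subgroup variable as main effect only | −10.93 | 0.72 |
| By arm, with subgroup variable | −15.07 | 1.00 |

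The analytic check predicts 0.60 × 15.12 = 9.07, close to 9.22.

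**Simulation B, log rate-ratio scale.** Negative binomial days, n = 520, the primary model's predictors, 5 donors, 5 imputations and 250 trials per scenario. Assumed: rate ratios 0.85 and 0.45 in two equal subgroups, so the true interaction is ln(0.45/0.85) = −0.636. Dispersion is 0.9 except where the plan's 2.12 is used. ρ is the assumed correlation of latent severity with work ability and with baseline absence. Company clustering was not simulated. Entries are ratios to the full-data estimate.

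| Scenario | As written, log (days) | Main effect only, log | Interaction added, log | Observed only, log |
|---|---|---|---|---|
| ρ = 0, 40% missing | 0.55 (0.58) | 0.59 | 0.86 | 0.97 |
| ρ = 0.4, 40% missing | 0.61 (0.65) | 0.60 | 0.93 | 1.01 |
| ρ = 0.6, 40% missing | 0.60 (0.66) | 0.60 | 0.92 | 0.99 |
| ρ = 0, missingness depends on arm and baseline absence | 0.53 (0.54) | 0.60 | 0.86 | 1.00 |
| ρ = 0.4, dispersion 2.12, 40% missing | 0.59 (0.63) | 0.61 | 0.85 | 0.99 |
| ρ = 0.4, 20% missing | 0.80 (0.83) | 0.80 | 0.97 | 1.01 |

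At about 40% missing the shrinkage is 39 to 47% on the log scale and 34 to 46% in days. At 20% missing it is 20% and 17%. Correlation of severity with the listed covariates, up to 0.6, does not remove it.

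**The case against.** The strongest reply is that the article never says the subgroup analyses use imputed data. Imputation is stated for the primary and secondary outcome analysis, and the per-protocol exemption need not mean that everything else is imputed. If subgroups are analysed on observed outcomes, this problem does not arise. That stands, and it makes the point conditional. A reader might infer that the plan already commits to biased subgroup estimates; the text does not support that.

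A reader might also infer that the imputation forces one common treatment effect. The article lists potential predictors and does not exclude interactions or imputation by arm. But imputing by arm without the subgroup variables would still not carry the subgroup difference, unless other covariates stood in for it.

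It is fair to add that the subgroup list is open, that these analyses lie outside the hierarchical testing sequence and the sample size calculation, and that deciding who should receive the programme is not among the stated aims. Details are also deferred to a later analysis plan. That deferral does not dispose of the point, because the article has already fixed a predictor list, and an analysis plan that follows it inherits the gap.

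Finally, Simulation A gave power of 58% on observed outcomes and 21% with imputation as written. These figures rest on an assumed 16-day interaction (34 − 18), as large as the whole planned main effect (42 − 26), so they should not be read as forecasts for this trial.

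**Conclusion.** The point holds in conditional form. The stated predictors are too narrow for the planned subgroup analyses. If those analyses are run on the imputed data, the estimated subgroup differences shrink by about the share of outcomes missing: roughly 34 to 47% at the planned 40% dropout and 17 to 20% at 20% missing.

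The proportion depends little on the assumptions varied here, but it scales with the missingness that actually occurs; 40% is only a planning rate. The absolute sizes in days depend on assumed subgroup effects that the article does not give.

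The primary intention-to-treat comparison is not touched, since treatment group is among its imputation predictors. This is an inexpensive improvement to exploratory analyses and does not threaten the trial's main conclusion.

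**What to change.** State in the analysis plan which data the subgroup analyses use, and choose one of these:

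1. **Impute separately by arm**, with each pre-specified baseline subgroup variable (for example PHQ-9, GAF, diagnosis versus subclinical, indication of treatment) in the predictor list.
2. **Impute jointly, including the variable and its interaction with treatment.** A main effect alone is not enough. This serves the same purpose as option 1, but it recovered 85 to 93% of the full-data log interaction at 40% missing in Simulation B, whereas imputing by arm recovered all of it in Simulation A. The two were not compared in the same set-up.
3. **Fit the subgroup interaction models to observed outcomes**, with the baseline covariates included.

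Table 1 lists GAF, diagnosis, indication and PHQ-9 for all participants, so no new data are needed. Where type of treatment means care received after randomisation, it should not be handled as a baseline subgroup variable in any of these options.

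The cost is a sentence and a few lines of code. Option 1 leaves fewer donors per arm and so gives somewhat wider intervals; in Simulation A its power was 47%, against 58% on observed outcomes. Option 3 relies on missingness being explained by the covariates in the model.

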#### Outcomes

##### Primary outcome

Days of sickness absence within the last 6 months at second follow-up will serve as the primary outcome. As in comparable previous studies [25, 37], days of sickness absence is chosen as the primary outcome due to its economic value and because it is a relevant parameter of psychotherapeutic and psychiatric rehabilitation measures. Days of sickness absence within the last 6 months will be collected as a self-reported item by standardised paper-and-pencil or online questionnaires during baseline and during follow-ups. This item was self-developed for this study. Participants will be asked whether they were absent from work for health reasons within the last 6 weeks with response options “yes” and “no”. If participants ticked “yes”, they will be asked about the number of days of sickness absence within the last 6 months excluding regular non-working days.

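### The named imputation predictors leave out the 9-month outcomes, so with 40% planned dropout the imputation gains little over complete cases and needs missing at random given baseline alone

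*Protocol article*

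**What the plan says.** Under Statistical methods, the protocol article assumes missing at random for the primary and secondary outcomes. Missing values are "replaced using multiple imputation based on predictive mean matching", "using the covariates of the primary and secondary outcome analysis as potential predictors".

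The two models behind that phrase are set out in the same section. The primary model has "Treatment group, days of sickness absence within the last 6 months before baseline, gender, age, subjective work ability at baseline as well as the centre", with company as a random effect. The self-efficacy model has "treatment group, self-efficacy at baseline, gender, age, subjective work ability at baseline as well as the centre as covariates", again with company as a random effect. Taken together, the named predictors are treatment, baseline absence, baseline self-efficacy, gender, age, baseline work ability and centre.

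The Abstract says that "participants will be followed up after nine (first follow-up) and fifteen (second follow-up) months". Under Primary outcome, the absence item "will be collected as a self-reported item by standardised paper-and-pencil or online questionnaires during baseline and during follow-ups". Main secondary outcomes says the same of self-efficacy. Sample size calculations plans with "Assuming dropout rates of 40" per cent. The only sensitivity analysis named is a per-protocol analysis without imputation.

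**The concern.** The absence item recalls 6 months. The 9-month answer therefore covers roughly months 3 to 9 (9 − 6 = 3), and the primary outcome covers roughly months 9 to 15 (15 − 6 = 9). The 9-month answer describes the period directly before the primary window and is the natural predictor of a missing 15-month value. The named set leaves it out.

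The validity of the primary estimate is at stake. Without the 9-month value, the analysis is valid only if dropout is unrelated to the 15-month outcome once baseline and arm are known. Dropout that follows the clinical course differently by arm would break that condition, and such dropout is conceivable here. Participants are not blinded to allocation. The intervention arm may have up to 17 sessions and the control arm has one. Treatment may end when symptoms ease, and the follow-up reminder is given in the last therapy session. A distorted primary result would also affect whether the formal self-efficacy test is reached, because that test follows only a significant primary result. The per-protocol analysis would not correct the problem, since it uses no imputation at all.

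**Working it through.** **1. How many values would be imputed.** From 310 evaluable and 40% dropout (Sample size calculations): 310 / (1 − 0.40) = 517, consistent with the stated 520. Then 520 × 0.40 = 208 primary outcomes could be imputed. The article does not say how many of these participants would be lost before or after month 9.

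**2. What the named set can do.** Let X be the named predictors, Y9 the 9-month value, Y15 the primary outcome, and R = 1 if Y15 is observed.
- As named, the plan needs P(R = 1 | X, Y15) = P(R = 1 | X).
- With the 9-month value it needs P(R = 1 | X, Y9, Y15) = P(R = 1 | X, Y9), which allows dropout to follow the 9-month course.

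If only Y15 is missing and X is essentially the covariate set of the analysis model, people without Y15 carry almost no information on Y15 given X. The imputed analysis then approximates the complete-case one. Two exceptions remain: baseline self-efficacy is outside the primary model and so acts as an auxiliary variable, and missing baseline covariates can be recovered.

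**3. Simulation.** Taken from the protocol: N = 520, about 40% missing, negative binomial dispersion 2.12. Assumed, because the documents do not give them: correlation 0.6 between months 9 and 15, baseline correlation 0.3, mean 9-month absence 30 against 40 days. Dropout related to 9-month absence had log-odds 0.8 per SD, and in the one-arm scenarios this applied to the intervention arm. Losses before month 9 were random. There were 200 runs per scenario with 10 imputations each. The imputation with the 9-month value let its slope differ by arm.

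Difference in log rate ratio from the analysis of full data:

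| Dropout mechanism | Dropouts with 9-month value | Complete cases | Imputation without 9-month value | Imputation with 9-month value | Gap between the imputations |
|---|---|---|---|---|---|
| Random | 50% | −0.001 | +0.047 | +0.038 | 0.009 |
| Equal in both arms | 50% | +0.010 | +0.061 | +0.058 | 0.003 |
| Equal in both arms | 100% | +0.016 | +0.070 | +0.063 | 0.007 |
| One arm | 25% | −0.082 | −0.034 | +0.017 | 0.051 |
| One arm | 50% | −0.122 | −0.071 | +0.027 | 0.098 |
| One arm | 100% | −0.208 | −0.167 | +0.020 | 0.187 |

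The Monte Carlo error of the differences from full data is at most 0.010. Under random or equal dropout, both imputations move by +0.04 to +0.07 because of the simple matching on a skewed count. This artefact is not part of the point and largely cancels in the last column.

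As rate ratios in the last row: 0.517 without the 9-month value, 0.623 with it, 0.610 with full data.

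**4. Closeness to complete cases.** Across scenarios, estimates from imputation without the 9-month value correlated 0.93 to 0.95 with complete-case estimates, with mean SE 0.167 to 0.181 against 0.162 to 0.176. Adding baseline self-efficacy (assumed correlation −0.2) moved the one-arm results only to −0.020, −0.055 and −0.155, a change of at most 0.016.

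**5. A second simulation, with no true effect.** One scenario was run: 60% of dropouts with a 9-month value, correlation 0.7, dropout tied to 9-month absence in one arm at log-odds 0.7 per SD. The planned imputation gave a rate ratio of 0.894, and the false-positive rate was 18–19%. With the 9-month value these were 0.97 and 7%.

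**The case against.** The article calls the covariates potential predictors, never says that they are the only ones, and leaves details to a statistical analysis plan to be written before database closure. Auxiliary variables are often listed there. This stands to the extent that the article does not prove the 9-month data will go unused. It does not remove the point: the article names the predictor set, and a plan that follows it inherits the weakness.

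Three stronger readings are tempting, and the documents do not support them.
- A reader might infer that the imputation adds nothing. It can use baseline self-efficacy and recover missing baseline covariates, so the gain is small rather than nil.
- A reader might infer that the primary result will be biased. Appreciable bias that the 9-month value could remove needs dropout related to the 9-month course, differently by arm, among people who returned a 9-month questionnaire. The documents report none of these, and 40% is a planning figure.
- A reader might take the word potential to allow a selection step that drops treatment group. Treatment is a covariate of both models, and no such step is described.

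The simulations also simplify. The check in steps 3 and 4 fitted only treatment and baseline absence, without the company random effect. The second simulation used log-normal Poisson counts and a log-link model with robust SE. The 18–19% false-positive rate belongs to one assumed scenario and is not a forecast.

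**Conclusion.** The point holds as a weakness in a stated method, not as a demonstrated bias. The named predictors omit two outcomes that the trial collects at month 9. At the planned dropout, the imputation therefore gains little over complete cases and depends on missing at random given baseline alone.

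The consequence ranges from negligible (a gap of 0.01 or less on the log scale under random or equal dropout) to about 0.05, 0.10 and 0.19 under one-arm dropout with 25%, 50% and 100% of dropouts having a 9-month value. In the one-arm scenarios simulated, the imputation without that value overstated the benefit. These sizes rest on the assumed correlations and dropout strength. For participants lost before month 9, the change gains nothing.

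**What to change.** Amend the imputation sentence, and carry it into the statistical analysis plan, along these lines: *The imputation model will include treatment group, all covariates of the primary and secondary models, and sickness absence and self-efficacy at the first follow-up as auxiliary variables; where these 9-month values are missing, they will themselves be imputed.* Stating that these variables are included, rather than potential, also removes any doubt about treatment group.

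Imputing separately by arm is optional, as is adding other 9-month measures such as the PHQ-9 and work ability. The schedule table is not shown, so 9-month collection of those two cannot be confirmed here.

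The cost is wording and a small change to the analysis program. Both 9-month outcomes are already collected, so no new data or participants are needed. The change should be fixed before the database is closed.

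### The sensitivity analysis that the article names (per-protocol, no imputation) cannot show whether the primary result depends on the missing-at-random assumption

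*Protocol article*

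**What the plan says.** Under Statistical methods, the protocol article sets a mixed negative binomial model on the full analysis set by intention to treat. The missing outcome "is assumed to be “missing at random" and is filled in by multiple imputation with predictive mean matching. The potential predictors are the covariates of the outcome models: for the primary outcome these include baseline absence, gender, age, baseline work ability and centre.

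One analysis carries the label of sensitivity analysis: "As a sensitivity analysis, an evaluation based on the per-protocol (PP) population will be performed". It is restricted to participants with no major violation of the protocol, and for it "no imputation of missing data will be performed".

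The sample size section gives "Assuming dropout rates of 40" per cent as the basis for raising 310 participants to 520. Statistical methods leaves further detail to an analysis plan to be written before database closure, which is not at hand.

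**The concern.** A sensitivity analysis helps when it changes one assumption and keeps the rest. This one makes two changes at once, from all randomised participants to a per-protocol set and from imputed to complete data, so a difference from the ITT result could come from either. The per-protocol set is also defined by what happens after randomisation. The intervention arm can have up to 17 sessions and the control arm has one, so the opportunity to deviate differs by arm.

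Agreement would be no more informative. A complete-case fit adjusted for the covariates that also drive the imputation needs essentially the same condition: given those covariates, non-response is unrelated to the unseen number of days. If that fails, both analyses are wrong in the same direction.

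The assumption matters in this trial. Participants know their allocation, the outcome is self-reported, and those who withdraw consent have no follow-up measurement. Residual dependence of non-response on current absence is plausible. The primary result also gates the confirmatory test of self-efficacy, so more than one conclusion hangs on it.

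**Working it through.** **Inputs** (Sample size calculations). Intervention mean 26 days: "may reduce days of sickness absence from 36 days/6 months to 26 days/6 months at follow-up". Control mean 42 days: "days of sickness absence will increase from 36 days/6 months to 42 days/6 months". Dispersion 2.12. Evaluable number: "assuming a two-tailed level of significance of 5%, a sample size of 310 participants with 155 participants for each group is required". Dropout 40%.

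**The plan's own figures.** 310/(1 − 0.40) = 516.7, so 517, rounded up to 520: reproduced. At that dropout, 0.6 × 520 = 312 outcomes are observed (156 per arm) and 0.4 × 520 = 208 are imputed. For the 310, the usual log rate-ratio formula gives n per arm = (1.960 + 0.842)² × (1/42 + 1/26 + 2 × 2.12)/ln(26/42)² ≈ 147. Power at 155 per arm is about 82%, close to the stated 80%.

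**Scenarios.** An arm's mean is 0.6 × (observed mean) + 0.4 × (mean among the missing). Power holds precision at 156 per arm and dispersion at 2.12.

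| Missing, intervention | Missing, control | Arm means | Rate ratio | Power |
|---|---|---|---|---|
| 26 (MAR) | 42 (MAR) | 26.0 vs 42.0 | 0.62 | 82% |
| 36 (assumed baseline) | 42 | 30.0 vs 42.0 | 0.71 | 53% |
| 42 (like control) | 42 | 32.4 vs 42.0 | 0.77 | 35% |
| 36 (+10) | 52 (+10) | 30.0 vs 46.0 | 0.65 | not computed |
| 26 × c | 42 × c | same factor in both | 0.62 | not computed |

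**Where significance is lost**, for an observed ratio of 0.62 and control dropouts at 42:

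- SE of the log ratio = √[(1/26 + 1/42 + 2 × 2.12)/156] = 0.166.
- Largest significant ratio = exp(−1.96 × 0.166) = 0.722.
- Intervention mean at that ratio = 0.722 × 42 = 30.3.
- Mean among the missing = (30.3 − 0.6 × 26)/0.4 ≈ 37 days, about 1.4 times the 26 assumed and close to the assumed baseline of 36.

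This point depends on the dispersion. The plan also states "The same standard deviation of 35 days/6 months will be expected for the control group", and an SD of 35 at means of 26 and 42 implies dispersions of 1.77 and 0.67, both below 2.12. With the SD used directly, SE = √[(35²/26² + 35²/42²)/156] = 0.127. The limit is then exp(−1.96 × 0.127) = 0.780, and the mean among the missing is (0.780 × 42 − 15.6)/0.4 ≈ 43 days. The range is therefore about 37 to 43 days.

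**Do the two missing-data methods fail together?** A simulation with 300 replicates used 520 participants, the planning means, dispersion 2.12, one baseline covariate and about 40% missing. Missingness was random in controls and rose with the outcome in the intervention arm. The mean rate ratio was 0.615 with full data, 0.489 with predictive-mean-matching imputation and 0.482 with complete cases. The two estimates correlated at 0.96. The dropout mechanism is an assumption. The complete-case fit used all randomised participants with an outcome, so it isolates the missing-data handling and does not model per-protocol exclusions.

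**The case against.** The strongest objection is that the article defers detail to an analysis plan, and delta-adjusted or control-based analyses are often specified there. That stands against a stronger reading that a reader might infer, namely that MAR goes unchallenged in this trial. The document supports only that the check it names does not challenge it.

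A second objection is that the article never says the per-protocol evaluation tests MAR, and per-protocol beside ITT is a conventional look at protocol violations. This is fair. Even for that purpose, though, dropping the imputation at the same time blurs the comparison.

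Third, 40% is a planning figure. Participants who stop treatment stay in the study and are reminded of follow-up; measurements cease only when consent is withdrawn. Actual missingness may be lower, and the document does not establish that 40% of outcomes will be missing.

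Fourth, MAR here is conditional on baseline absence and work ability, so dropout driven by those is already handled. Only dependence on the unseen follow-up value remains.

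Fifth, the reason for worry, that people with long absence stop answering, applies to both arms. Worsening the intervention arm alone is a stress test, and the symmetric rows show how little changes otherwise. All of this narrows the point. None of it makes the named analysis informative about missing data.

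**Conclusion.** The point holds in this limited form: the one sensitivity analysis named in the article mixes two changes, selects after randomisation, and shares the primary analysis's MAR condition, so neither agreement nor disagreement says whether the conclusion depends on that condition.

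Its possible size ranges from nothing (equal proportional worsening in both arms, ratio 0.62), through 0.65 (both arms 10 days worse), to 0.71 or 0.77 if only intervention dropouts return to baseline or resemble controls. At 0.77 the 38% reduction becomes 23%. Significance is lost when missing intervention participants average about 37 days with the plan's dispersion, or about 43 days with its SD.

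This rests on 40% missing in each arm, an observed result equal to the planning means, and precision held at 156 completers per arm. A reader might take 0.77 as the likely true effect. The documents do not support that, since nothing in them says how dropouts will fare.

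**What to change.** Name as the missing-data sensitivity analysis an ITT multiple imputation that departs from MAR, either delta-adjusted (tipping-point) or control-based, and report where significance is lost.

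- Vary the shift separately by arm and include equal shifts. The planning means suggest natural anchors: 10 days takes intervention dropouts to the assumed baseline of 36, and 16 days takes them to the control mean of 42.
- Prefer shifts in days to multipliers. A multiplier leaves imputed zeros at zero, and a factor as large as 2.0 can exceed the days available.
- Cap imputed days at the participant's possible working days in six months, because the item excludes regular non-working days. Report the mean shift that remains after capping.
- Keep per-protocol as a supplementary analysis with the same imputation as the primary analysis, so that only the population changes.

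This needs no new data. It can go into the analysis plan, preferably before outcome data by arm are seen. The cost is a few more imputation runs and a result that may look less robust.
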